## Abstract

**Background:**

Carpal tunnel syndrome is the most common neuropathy in the upper extremity, resulting from the compression of the median nerve at wrist level. Clinical studies are essentials to present evidence on therapeutic resources use at early restoration on peripheral nerve functionality. Low-level laser therapy has been widely investigated in researches related to nerve regeneration. Therefore, it is suggested that the effect of low-level laser therapy associated with other conservative rehabilitation techniques may positively affect symptoms and overall hand function in compressive neuropathies such as carpal tunnel syndrome. The aim of this study is to evaluate the effectiveness of low-level laser therapy in addition to orthoses therapy and home orientations in patients with carpal tunnel syndrome.

**Methods/Design:**

Patients older than 18 years old will be included, with clinical diagnosis of carpal tunnel syndrome, excluding comorbidies. A physiotherapist will conduct intervention, with a blinding evaluator. Randomization will be applied to allocate the patients in each group: with association or not to low-level laser therapy. All of them will be submitted to orthoses therapy and home orientations. Outcome will be assessed through: pain visual analogic scale, Semmes Weinstein monofilaments™ threshold sensibility test, Pinch Gauge™, Boston Carpal Tunnel Questionnaire and two point discrimination test.

**Discussion:**

This paper describes the design of a randomized controlled trial, which aim to assess the effectiveness of conservative treatment added to low-level laser therapy for patients with carpal tunnel syndrome.

**Trial registration:**

Brazilian Clinical Trials Registry (ReBec) - 75ddtf / Universal Trial Number: U1111-1121-5184

## Background

Carpal tunnel syndrome (CTS) is the most common neuropathy in the upper extremity, resulting from the compression of the median nerve at wrist level. The compression is related with increased pressure at the carpal tunnel, elicited by the expansion of the structures contained within. Inflammatory or hemorrhagic conditions affecting the wrist, polyneuropathies, diabetes, rheumatoid arthritis, hypothyroidism, pregnancy and other hormonal alterations are also related with CTS [1-3].

The diagnosis of CTS is based on patient history and specific physical examination, and confirmed by complementary exams such as electroneuromyography. It affects mostly women in their fourth to seventh decade, presenting painful numbness at the median nerve path, often relieved with shaking the hands repeatedly (Flick’s sign) [4,5].

In order to properly assess the relief of symptoms and functional outcomes after conservative or surgical treatment of CTS, health professionals search for evaluation methods that are valid and reliable. Objective and subjective parameters must be taken into account, like measurements of pain, grip and pinch strength, sensory assessment, dexterity and patient perceived outcomes, through self-reported measures like the Boston Carpal Tunnel Questionnaire (BCTQ) [6]. The association of objective and subjective measures provides a better understanding about the physical and functional impact of CTS [7,8].

There are numerous instruments for sensory evaluation of the hand described in the literature [9-13]. Of all methods available, two point discrimination (2PD) and assessment of touch thresholds with Semmes Weinstein Monofilaments are most widely used in patients with CTS [9].

Pinch strength can be accessed through a dynamometer, such as the Pinch Gauge^TM^. Patients with CTS usually present diminished pinch strength, mostly in severe cases. The assessment of pinch strength can also help with determination of CTS severity degrees [14]. Amongst the available pinches to be assessed, pulp-to-pulp pinch seems to be the most responsive for CTS patients, due to the fact that is performed by muscles innervated by the median nerve [15].

The conservative treatment of CTS is based on non-steroidal anti-inflammatory drugs, local steroid injections and wrist splinting [16]. Other modalities like exercise therapy, therapeutic ultrasound and low level laser therapy are also described in the literature, being commonly used for the conservative treatment of CTS [17].

Patient education, with orientations about body posture while performing different activities of daily living are an important part of the rehabilitation program for conservative treatment of CTS. The patient must avoid repetitive wrist movements; especially wrist flexion associated with prolonged grip activities. Patient education booklets have showed great efficacy as a complement of treatment in many upper limb disorders [18].

Different types of wrist orthoses with variations in immobilization angles are reported in the literature as effective for CTS treatment. Orthoses is the most widely used method of conservative treatment, and its effectiveness is based on the principle that adequate positioning the wrist minimizes the compression of the median nerve, maintaining an optimal position to preserving the volume of the carpal tunnel and providing rest to the structures that go through the wrist, thus relieving the symptoms of CTS. The orthoses should be worn at night, although for patients with severe symptoms it can be also used during the day (full time or intermittent). In certain cases a orthoses that also immobilizes the metacarpophalangeal joints with 20 to 40 degrees of flexion can be prescribed, in order to minimize painful symptoms due to lumbrical muscles hypertrophy that contributes to the increased pressure at the carpal tunnel [19].

Among the available resources, studies with low level laser therapy (LLLT) demonstrated effectiveness for conservative treatment of CTS, probably due to LLLT biophysical effect in neural tissue that can facilitate its regeneration [20].

Some studies have focused on LLLT application in peripheral nerve injuries in the last decades. The first report of LLLT use with this purpose dates from the late 70’s by Rochkind et al., and since the early 80’s the scientific interest in this subject has increased, with papers demonstrating positive effects of LLLT in nerve cells regeneration [21,22]. From this moment on, other experimental studies were conducted in order to understand the role of that therapeutic modality in peripheral nerve regrowth and functional rehabilitation after nerve injuries [23-28]. Therefore, it is suggested that the effect of LLLT associated with other conservative rehabilitation techniques may positively affect symptoms and overall hand function in compressive neuropathies such as CTS.

## Methods/Design

The trial is a prospective randomized clinical trial, adhered to CONSORT guidelines, with the objective of assessing the effectiveness of conservative treatment with LLLT for patients with CTS, associated or not with other modalities like wrist orthoses and a patient education booklet.

### Ethics

The present study was approved by the Ethics Committee at the Hospital Clinics Faculty of Medicine of Ribeirão Preto (process number 7107/2010). All subjects recruited will sign an informed consent form.

### Eligibility criteria

Eligibility criteria are age over 18 years, clinical diagnosis of CTS, with no history or current associated upper limb injuries due to orthopedic, neurologic or rheumatologic disorders (Figure 1).

**Figure 1 F1:**
[figure not shown]
Carpal tunnel syndrome treatment flowchart.

### Recruitment

Sixty patients with clinical and Electroneuromyography (EMG) diagnosis of CTS referred from a University Hospital will be recruited for our study. After an initial assessment, all patients that fit the inclusion criteria will be randomized to two different groups through a computer-generated list unknown to the recruiters, as follows:

• Control group. Conservative treatment with night splinting and patient education for 6 weeks.

• Low-level laser intervention group. Conservative treatment with night splinting, patient education and low-level laser therapy for 6 weeks (12 therapy sessions).

Hand surgeons will conduct clinical diagnosis and an experienced hand therapist will assess the outcomes, whose will be blinded to group assignment.

### Outcome measures

Assessment will be conducted pre and post intervention based on items related to pain, sensibility, functionality, symptoms and pinch muscle strength. Pain will be assessed by the pain visual analogic scale, sensibility by Semmes Weinstein monofilaments (Sorri^TM^, Bauru, Brazil) to detect threshold cutaneous sensibility and gnosis tactile through 2PD (North Coast, USA). Isometric pinch strength will be assessed through a dynamometer, Pinch Gauge ^TM^ (North Coast, USA). BCTQ [6] will be used as a specify disease functional and symptom related self-reported measure.

### Interventions

An experienced hand therapist will perform all interventions, in Rehabilitation Center of Clinical Hospital of the Medical School of Ribeirão Preto, University of São Paulo, Brazil.

#### Home orientations

##### Patient education booklet

A patient education booklet will be written specially for this study. It contains home and work orientation with emphasis in preventing activities which put the wrist in risk of median nerve compression at carpal tunnel, like excessive flexion and repetitive movement with the fingers or prolonged isometric sustained grip.

#### Wrist orthoses

The prescribed orthoses design will be in neutral wrist position, called immobilization splint, type 0, with the aim to reduce carpal intratunnel pressure and prevent from flexion posture (Figure 2), during night for 6 weeks.

**Figure 2 F2:**
[figure not shown]
Wrist neutral immobilization splint, type 0.

#### Low-level laser therapy

A gallium-indium-phosphorus-aluminum (AlGaInP) laser emitter – Laserpulse^TM^, will be used (Ibramed™, Amparo, Brazil), with the following parameters: with wavelength 660 nm, mean power 30 mW, continuous regime and area of bean of 0, 06 cm^2^. The laser irradiation will be done with fluency of 10 J/cm^2^, energy (E) of 0.6 J, and exposure time of 20s for point, totaling six points of irradiation over the carpal tunnel. The laser will be positioned at an angle of 90° to the skin, according to the contact point technique. The patients will be irradiating twice a week, for 6 weeks (12 therapy sessions).

Gauging the laser emission will be conducted initially and after completion of the experiments.

### Statistical analysis

#### Data-analysis

A linear mixed-effects model will be used to compare the results. This model assumes individuals as random effects and groups as fixed effects, using time variation and interaction between them for calculating mean, standard deviation, and coefficient of variation. A 95% confidence interval and 5% significance level will be adopted. Linear mixed-effect models (random and fixed effects) are typically used for the analysis of grouped data from the same individual when independence supposition between observations within the group is not adequate.

This model assumes that the residual value from the difference between the predicted and observed values has a normal distribution, with zero mean and constant variance. In those situations where this supposition was not observed, the variable response was converted. The model was adjusted with SAS version 9.0 software.

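### One normal-error model covers every outcome and lets the observed residuals set the analysis scale, on which the group-by-time effect depends

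*Protocol article*

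**What the plan says.** The Data-analysis section of the protocol article names a single method for all outcomes: "A linear mixed-effects model will be used to compare the results". Its structure is given as follows: "This model assumes individuals as random effects and groups as fixed effects, using time variation and interaction between them". The residual is assumed to be one that "has a normal distribution, with zero mean and constant variance". The only provision for failure of that assumption is "In those situations where this supposition was not observed, the variable response was converted". On inference the section adds "A 95% confidence interval and 5% significance level will be adopted".

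The Outcome measures section lists what this model has to cover: pain on a visual analogue scale (VAS), "sensibility by Semmes Weinstein monofilaments", two-point discrimination (2PD), pinch strength by dynamometer, and the Boston questionnaire (BCTQ). Each is measured before and after treatment. No outcome is given a different model.

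The article does not name the conversion, the check that triggers it, or the scale on which the effect is then reported. It also does not say how the monofilament and 2PD results are scored.

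**The concern.** A protocol article may leave detail to an analysis plan. This one does more than stay silent: it states a rule under which the response scale follows from residuals that can be examined only once outcome data exist. An analysis plan that carried the sentence over would inherit the problem.

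Two consequences follow.

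- **The effect changes meaning.** With two groups and two visits, the term that carries the treatment comparison is the group-by-time interaction, and its size, even whether it is zero, depends on the scale. Converting the response therefore does more than tidy the residuals. It can change what is being estimated, and the estimate is no longer in VAS or BCTQ units.
- **The remedy may not work where it is most needed.** A monotone conversion relabels the values of a step-scored measure but leaves the ties and the pile-up in place. If the monofilament threshold is recorded in a few steps, its residuals stay non-normal after conversion, and the plan offers nothing else.

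At stake are a result that readers can interpret, power, and assurance that the scale was not chosen with the results in view.

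**Working it through.** **Inputs from the protocol article.** One mixed model with group, time and their interaction, conversion if residuals are not normal, and a 5% level (Data-analysis). Sixty patients in two randomised groups (Recruitment). One assessment before and one after treatment (Outcome measures). The plan gives no figure on this point that could be reproduced.

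**Assumptions.** 30 patients per group (the ratio is not stated), a two-sided test, and the outcome shapes given in step 2.

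**Step 1: dependence on scale.** Take illustrative VAS values of 60 to 40 in control and 50 to 30 with laser, treated as the typical patient in each group.

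- Raw: (30 − 50) − (40 − 60) = −20 + 20 = 0.
- Square root: (5.477 − 7.071) − (6.325 − 7.746) = −1.594 + 1.421 = −0.17.
- Log: ln(30/50) − ln(40/60) = −0.511 + 0.405 = −0.105; exp(−0.105) = 0.90.

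The same data show no difference in absolute change and a 10% relative benefit. The reverse also occurs. With 6 to 3 in control and 4 to 2 with laser, the raw interaction is (2 − 4) − (3 − 6) = 1, while the ratio is (2/4)/(3/6) = 1.00. Both examples need unequal baselines, which after randomisation arise only by chance.

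**Step 2: simulation.** With two complete visits, the group-by-time test of a random-intercept model equals a t-test on change. Trials were simulated with a latent pre-post correlation of 0.5, using 20,000 trials per setting; the normality checks and the residual-triggered rule used the first 3,000. Three shapes were assumed: a skewed six-level score, a log-normal score, and a score bounded at 0 and 10 (0.5 added before log or reciprocal). The residual-triggered rule was taken as: Shapiro test on the residuals, and log if p < 0.05.

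| | Six-level | Log-normal | Bounded |
|---|---|---|---|
| No effect: raw, significant | 5.1% | 4.8% | 5.1% |
| No effect: log, significant | 5.0% | 5.1% | 4.9% |
| No effect: residual-triggered rule | 5.2% | 6.1% | 5.0% |
| No effect: best of four scales, chosen after seeing results | 7.8% | 9.6% | 8.0% |
| No effect: residuals fail normality, raw | 93% | 83% | 4% |
| No effect: residuals fail normality, after log | 86% | 4% | 66% |
| Latent effect 0.5 SD: power, raw | 28% | 25% | 47% |
| Latent effect 0.5 SD: power, log | 34% | 48% | 48% |
| Latent effect 0.5 SD: raw and log disagree on significance | 12% | 27% | 16% |

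The four scales are raw, square root, log and reciprocal. The simulation error of a 5% rate is √(0.05 × 0.95/20,000) = 0.15 percentage points, or 0.4 points with 3,000 trials.

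**Step 3: reading.** A scale fixed in advance keeps the error rate at about 5% or below, and a mechanical residual-triggered rule stays close to that. Inflation to roughly 8–10% needs a choice made with the results in view. When there is a real effect, the verdict on significance differs between raw and log in 12% to 27% of trials. For the six-level score, the log leaves the residuals non-normal in most trials.

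**The case against.** The strongest reply is that this is a condensed article, and that the type of conversion and the diagnostic are details an analysis plan would supply. That holds for the missing details. It does not cover the rule itself, which ties the scale to the observed residuals and offers no other remedy.

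A reader might also draw stronger conclusions, which the documents do not support:

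- **That the rule manufactures a treatment effect or invalidates the test.** The stated trigger is the residuals, not the treatment result, and simulated that way the error rate was 5.0% to 6.1%. The linear test also kept its size on the six-level score. A spurious difference needs chance baseline imbalance or a scale picked after seeing results. The text does not describe such picking, although it does not exclude it.
- **That the scale is chosen after unblinding.** The section is silent on timing and on blinding of this decision.
- **That the sensibility scores are ordinal.** No scoring is given. A few-step record is plausible for a set of monofilaments; 2PD may be recorded as a distance.
- **That pain scores of zero break the analysis.** This would apply to a plain log, and no log is named. A square root or a shifted log is defined at zero.
- **That converted results can never be set against a clinically relevant difference.** The article sets no such difference, and back-transformation or parallel untransformed reporting is not excluded.

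One further objection stands as a cost. For a strongly skewed outcome the raw scale can lose power: 25% against 48% in the log-normal case.

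**Conclusion.** The point holds in limited form. The protocol makes the analysis scale of every outcome depend on the observed residuals, and the group-by-time comparison it relies on can give a different answer on a different scale: 0 raw against a ratio of 0.90 on the log scale in the worked example. If the monofilament threshold is step-scored, conversion does not restore the assumption it is meant to restore.

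The harm is to interpretation, to power and to protection against post hoc choice of scale, not to the validity of the test. The arithmetic depends only on the illustrative means and their baseline imbalance. The simulated percentages depend on the assumed shapes, the correlation of 0.5 and 30 patients per group, and show order of magnitude only. The change is worth making because it is cheap and removes the ambiguity.

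**What to change.** State the primary analysis scale for each outcome before any outcome data are seen.

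- **VAS, BCTQ and pinch strength:** the untransformed difference between groups after treatment, adjusted for the baseline value already collected, with a robust or bootstrap 95% confidence interval. Baseline adjustment also deals with the chance imbalance that drives the worked example.
- **Monofilaments, and 2PD only if it is step-scored:** a baseline-adjusted ordinal or rank-based analysis. State the scoring of both measures so that the choice can be judged. If 2PD is recorded as a distance, an ordinal model is not called for.
- **Conversion:** remove it from the primary analysis and keep it, if wanted, as a labelled sensitivity analysis.

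The cost is analysis wording and a little programming; the sixty patients, the assessments and the treatments are unaffected. Some power may be lost if an outcome is strongly skewed. The 25% against 48% in the simulation indicates how much that could be, but it comes from change scores; the baseline-adjusted analysis proposed here was not simulated. Step-scored outcomes would no longer be reported as means, and an ordinal model brings its own assumption and may meet sparse categories with sixty patients.

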## Discussion

Despite the widespread use of LLLT as one of the most popular and commonly used modalities in the field of physiotherapy, there is still limited evidence of its effectiveness. Only a few RCTs have investigated the effect of LLLT in treating patients with CTS; often with varying methodology qualities and have not been able to provide evidence regarding its usefulness.

The advantages of this study would be comparing the LLLT for patients with CTS, associated or not with other modalities like wrist orthoses and a patient education booklet to provide some evidence regarding this indication and use.

## Abbreviations

CTS: Carpal Tunnel Syndrome; BCTQ: Boston Carpal Tunnel Questionnaire; 2PD: Two point discrimination; LLLT: Low level laser therapy; EMG: Electroneuromyography; AsGaIP: Gallium– indium-phosphorus-arsenide; RCT: Randomised clinical trials.
